**Fig. 1 Fig1:**
[figure not shown]
Schedule of enrollment, interventions, and assessments. X: discrete point in time during which an event occurs. : continuous period over which an event occurs

Data from baseline and follow-up surveys is collected using handheld tablets on which an electronic data collection form is programmed. The program includes range and consistency checks, and automatic skip patterns. Backcheck surveys consisting of a subset of the survey questions are administered to randomly selected participants to ensure data quality. Tablets are sent to the field office on a regular basis where the data is removed for secure storage.

### Study timeline

The first wave of enrollment into the study began in February 2013, and enrollment of the final wave (wave 6) was completed in November 2014. Follow-up data collection on wave-2 enrollees began in July 2015. Data collection for all waves is expected to be completed by November 2016.

### Data analysis plan

Data will be analyzed on an intent-to-treat basis, meaning that non-compliers (participants who refused to allow their stored maize to be tested and swapped, or who did not purchase any aflatoxin-safe maize from stockists) are treated as part of the intervention group for purposes of analysis. Both unadjusted and adjusted analysis of covariance (ANCOVA) models will be used to assess the impact of the intervention, controlling for mothers’ blood aflatoxin level at enrollment. In all models, standard errors will be clustered at the village level to account for within-cluster correlation of outcomes.

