The impact of chronic aflatoxin exposure on child growth is not well-understood. In Ghana, women exhibiting high serum aflatoxin levels – a marker of having been exposed over the previous 2 to 3 months – at delivery were more likely to have a low-birth weight baby; no association was found with having a baby small for gestational age or with preterm birth [5]. The analysis controlled for socio-economic status (SES), but no details were provided on how this was done, making it difficult to evaluate whether confounding was adequately controlled for. A study in the Gambia showed that exposure occurred before the linear growth retardation: serum aflatoxin levels in pregnant women and in infants at 16 weeks of age were strong predictors of linear growth during the first year of life. Cord blood levels were not associated with birth weight or length [6]. The Gambia study did not control for SES. A study in Benin and Togo found that the serum aflatoxin level was 30–40 % higher in stunted children 1 to 5 years of age than in non-stunted children, after controlling for confounders including SES, child age, and sex. Details on the measure of SES were not provided by the authors [7]. Finally, the same authors studied the linear growth of 200 Togolese children 16 to 37 months of age over an 8-month period. Children in the highest serum aflatoxin albumin quartile grew 1.7 cm less than children in the lowest quartile, after controlling for age, sex, baseline length, and SES. As in the previous study, the authors did not provide details on the SES measure used [8].

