Although these findings are generally consistent, none of the studies used a controlled intervention methodology. As a consequence, it is not clear to what extent the association between aflatoxin and child linear growth was confounded by factors such as household SES, child morbidity and dietary intake. For example, it may be the case that poor households are less able to afford proper post-harvest technologies to ensure that maize is fully dried and properly stored; this would potentially lead to poorer households consuming own-produced maize with higher levels of aflatoxin contamination. Poorer households may also consume more aflatoxin as a result of purchasing lower-quality maize. Poorer households also have lower dietary intake and diversity, poorer sanitation, and higher morbidity, which may manifest in stunted children, thereby inducing a spurious correlation between aflatoxin and child linear growth.

The specific objective of this study is to determine whether consumption of aflatoxin has a direct causal impact on child linear growth during the period from before birth to age 24 months. The hypothesized pathway is a biological one: human and animal studies indicate that aflatoxin causes immunosuppression (which in turn can lead to repeated infections and, consequently, growth retardation in young children), impairs protein synthesis, and causes changes in the hepatic metabolism of micronutrients [4]. It has also been suggested that aflatoxin, together with fumonisin and deoxynivalenol (two other mycotoxins commonly found in maize and groundnuts), mediate intestinal damage similar to environmental enteropathy [9]. This condition is known to lead to chronic systemic immune activation and malabsorption of nutrients, which in turn may lead to growth retardation.

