### Sample size

To determine sample size, the minimum detectable effect (MDE) for exposure to treatment for the full 24-month period was set to 0.3 length-for-age Z-score (LAZ), based on the magnitude of effect sizes that have been obtained with known effective nutrition interventions [16]. This was then adjusted for partial exposure to the intervention of participants recruited in the first year of the study (prior to introduction of the stockist component) to give an MDE of 0.281.

Sample size calculations were performed to achieve an alpha of 0.05 and power of 80 % to detect a difference of means in LAZ between children in intervention and control villages using a 1-sided test. Based on anthropometric data collected in similar conditions, the standard deviation of the LAZ of children was assumed to be 1.28. Assuming an intra-cluster correlation for LAZ of 0.05, attrition of 9 %, and that 15 % of variation in the outcome would be explained by baseline variables, the estimated total number of participants required to achieve the study objectives was 924 across 56 villages

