### Eligibility and recruitment of participants

Enrollment of participants within these villages was conducted by the African Population and Health Research Center in 2013 and by Innovations for Poverty Action in 2014. Within each of the study villages, enrollment into the study was conducted in 6 waves, each 4 months apart. In each wave, women in the fifth to final month of pregnancy (by the woman’s estimate) were recruited to participate in the study. Scouts employed by the data collection firm identified pregnant women in the study area before the survey team arrived. This was done 6 times over the course of recruitment, at 4-monthly intervals. Informed consent was obtained from all participants as follows. The consent form, included as Additional file 2, was read to each potential participant by an enumerator at the initial visit. The participant was then asked to sign the document if he or she agreed to participate. All pregnant women who gave informed consent in this way were enrolled in the study. The number of recruitment waves required to attain an adequate sample size was calculated using birth rates from 2008 to 2009 Kenya Demographic and Health Survey and populations of the study villages from the 2009 Kenya Census.

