The stockist component of the intervention was introduced after trial commencement, in January–February 2014, in response to the observation that many households were accessing the majority of the maize they consumed through the market. This was unexpected and arose due to an unusually poor maize harvest in the study area in 2013. Household maize purchases are typically small and frequent, so the swapping intervention was missing a large portion of maize consumed. In the stockist intervention, Caritas Meru supplies maize containing less than 10 ppb aflatoxin to at least one shopkeeper in each of the intervention villages. In geographically larger villages, safe maize is supplied to multiple shopkeepers to ensure this maize is accessible to all study participants. Participating households are encouraged to purchase this tested maize, which is offered at the lowest price of maize currently for sale in the village. This encouragement is through an initial village meeting, as well as the monthly swapping visits. Participants have been provided with a laminated ID card displaying their name and unique identifying number. To ensure that an adequate supply of safe maize is available to study participants, stockists are asked to sell maize only to those presenting a study ID card, and to record all sales in a tracking form which includes a field for the household unique identifying number.

Participants in villages assigned to the intervention group were consuming untested, purchased maize for up to 12 months before the stockist component of the intervention was introduced, half of the study duration of 24 months. Due to the risk that these participants were exposed to the full intervention for an insufficient length of time to have an impact on the primary outcomes of interest, an additional wave of recruitment was added to replace this wave of recruits. Wave-1 households in the intervention group continued to receive the intervention for a 2-year period, according to the original protocol, but this group will be excluded from follow-up data collection.

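### Primary ANCOVA models name no enrollment-wave term, although sampling season differs by wave; wave indicators would remove avoidable noise, chiefly in serum aflatoxin

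*Protocol article*

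**What the plan says.** Under Data analysis plan the protocol states that "Both unadjusted and adjusted analysis of covariance (ANCOVA) models will be used to assess the impact of the intervention". It adds control for the mother's blood aflatoxin at enrollment and village-clustered standard errors. No other covariate is named there. Outcomes and data collection mentions SES, food consumption and child-feeding data as further controls, meant to reduce residual noise. Wave appears in neither place.

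Other sections show what changes with wave:

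- **Timing.** Eligibility and recruitment describes six waves, 4 months apart, inside each study village. Outcomes and data collection sets follow-up at 24 months after enrollment.
- **Serum window.** Background describes serum aflatoxin as "a marker of having been exposed over the previous 2 to 3 months". Child serum is one of the two primary outcomes, with LAZ at 20–24 months.
- **Intervention content and harvest.** Under Intervention: "The stockist component of the intervention was introduced after trial commencement", in January–February 2014, after an unusually poor 2013 harvest had moved households toward purchased maize.
- **Wave 1.** The same section says that an extra wave was recruited to replace wave 1, and that wave-1 intervention households are left out of follow-up.

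**The concern.** A marker that looks back 2–3 months, sampled in waves 4 months apart, gives adjacent waves windows that do not overlap. The mother's value at enrollment and the child's value two years later then carry season and harvest-year differences that have nothing to do with arm.

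Without a wave term, two things follow. The between-wave part of the outcome variance stays in the residual. The slope on maternal serum also mixes differences between seasons with differences between households sampled in the same season, which makes it a weaker baseline adjuster. Both matter most for serum.

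There is a second, conditional issue. If the arms differ in wave mix, wave differences pass into the arm contrast. The trial is not blinded, recruitment continued after swapping began in July 2013, and 28 villages per arm gave 687 and 536 households. The wave mix by arm is not given.

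**Working it through.** **1. Reproduce the stated sample size.** Inputs from the Sample size section: "Sample size calculations were performed to achieve an alpha of 0.05 and power of 80" per cent; a comparison "between children in intervention and control villages using a 1-sided test"; effect 0.281; SD 1.28; ICC 0.05; 15% of variation explained at baseline; attrition 9%; 56 villages.

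With m analysed children per village and the 15% applied to the between-village variance:

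SE = √(4 × SD² × [ICC × (1 − R²) + (1 − ICC)/m] / 56)

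At m = 15:
- bracket: 0.05 × 0.85 + 0.95/15 = 0.0425 + 0.0633 = 0.1058
- SE = √(4 × 1.6384 × 0.1058 / 56) = 0.1113
- MDE = 0.1113 × 2.522 (sum of the t quantiles on 54 df) = 0.2807
- power at 0.281 = 80.2%
- 56 × 15 = 840, and 840/0.91 = 923.1, rounded up to 924

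The stated 924 is reproduced. The protocol does not say where the 15% enters. Applying it to the individual-level variance also leads to m = 15.

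**2. Add a wave term for LAZ.** Let wave explain a share w of the total variance. The document gives no value, so w is an assumption. The term (1 − ICC)/m becomes (1 − ICC − w)/m.

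| w (assumed) | Power at 924 | Required N (unrounded m) |
|---|---|---|
| 0 | 80.2% | 915 |
| 1% | 80.4% | 906 |
| 2% | 80.6% | 896 |
| 5% | 81.3% | 867 |
| 10% | 82.4% | 819 |

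**3. Check for bias.** Simulation of 56 villages × 15 children, with each child's wave drawn from five equally likely waves in both arms, and with waves 2 and 3 losing 7 and 3 of 24 months of full exposure. The mean estimate was the same without and with wave indicators: 0.277 and 0.277 at w = 2%, 0.275 and 0.275 at w = 10%. The empirical SE fell by about 0.7% (w = 2%), 1.8% (5%) and 3.5% (10%). This setup expects the same wave mix in both arms, so it does not test a systematic difference in mix.

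**4. What an unequal mix could do (illustration only).** Assume that the 536 control households spread evenly over six waves (89.3 each) and that all 151 surplus intervention households (687 − 536) fall in waves 4–6. Among waves 2–6:
- control share in waves 4–6: 268/446.7 = 60%
- intervention share: (268 + 151)/(446.7 + 151) = 70%

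With an assumed gap of 0.3 LAZ between waves 2–3 and waves 4–6, the contrast shifts by 0.10 × 0.3 = 0.03. That is 11% of 0.281 and about a quarter of the SE of 0.111.

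**5. Serum.** The document gives no variance, ICC or seasonal spread for serum, so no figure can be computed.

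**6. Dilution from the late stockist start.** The Sample size section states that "the minimum detectable effect (MDE) for exposure to treatment for the full 24-month period was set to 0.3 length-for-age Z-score (LAZ"), then lowers it to 0.281, which is 93.7% of 0.3. With five equal waves (assumed), and waves 2 and 3 losing a and b months, the diluted effect is 0.3 × [1 − (a + b)/(24 × 5)]:
- a = 6, b = 2: 0.280
- a = 7, b = 3: 0.275
- a = 8, b = 4: 0.270

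The stated allowance is about the right size.

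**The case against.** **The omission is inferred from silence.** The article does not list the adjusted model's covariates, and a full analysis plan may include wave. This stands as a limit on the point, which is an improvement to what the article names and not a proven error. It has less force for the model called unadjusted, for which the text names maternal serum alone.

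**The sampling windows are not all separate.** Waves 4–6 get an additional visit 24 months after wave 3, and waves 12 months apart (2 and 5, 3 and 6) share a calendar season. Both are true. But the additional visit comes 20, 16 and 12 months after enrollment for waves 4, 5 and 6, when the children, unborn at enrollment, are mostly below the 20–24 month age of the primary outcomes. Waves a year apart also fall in different harvest years.

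**Wave is crossed with village and arm.** This stands. Shared season effects largely cancel from the contrast, and step 4 rests on two assumed inputs.

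A reader might infer four stronger claims that the document does not support:

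- *The change of data collector contaminates the outcomes.* Enrollment was run by one organisation "in 2013 and by Innovations for Poverty Action in 2014", but this is stated for enrollment only. It could touch the maternal covariate; nothing shows that it reaches outcomes measured on children at follow-up.
- *A wave term would restore the prenatal effect.* The objective is a "direct causal impact on child linear growth during the period from before birth to age 24 months", and the early retained waves had little prenatal access to stockists. A wave main effect cannot remove that dilution, and the 0.281 already allows for partial exposure.
- *A contrast of waves 2–3 with waves 4–6 would settle the matter.* With about 371 and 557 analysed children and village effects assumed to cancel, its MDE is 2.487 × 1.28 × √(0.85 × 0.95) × √(4/371 + 4/557) ≈ 0.38 LAZ. The expected difference is about 0.3 × 5/24 ≈ 0.06.
- *Wave 1 is confounded with arm.* Only wave-1 intervention households are said to be excluded. But Study timeline has follow-up beginning with wave 2 in July 2015, and Trial status says that follow-up had not begun at submission, by when wave 1 would already have been due (about February 2015). This suggests that wave-1 controls were not followed either.

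**Conclusion.** The point holds as a modest, nearly free gain in precision and as protection against unequal wave mix; no bias is demonstrated. For LAZ the gain is about 0.2 to 2.2 power points, resting on an assumed 1% to 10% wave share of variance and on the calculation that reproduces 924. For serum, where a 2–3 month marker meets 4-monthly waves and a poor harvest year, the gain is plausibly larger but cannot be sized. Whether wave mix differs by arm cannot be known from the household totals, and the 0.03 LAZ shift is only an illustration. The all-wave intent-to-treat estimate and the 0.281 are not in question.

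**What to change.** In Data analysis plan, state that every primary model for LAZ and for serum, including the one called unadjusted, contains indicators for enrollment wave, and that the all-wave intent-to-treat estimate remains primary.

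The cost is one sentence. Households were enrolled by wave, so no new data are needed. Five retained waves use four degrees of freedom at child level and none between villages.

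No contrast between early and late waves should be added as a remedy. If an estimate for waves 4–6 alone is reported, label it exploratory. With about 612 of 1,223 households (half, assuming six equal waves) and 9% attrition, m = 557/56 = 9.95, SE = √(4 × 1.6384 × [0.0425 + 0.95/9.95]/56) = 0.127, and the MDE is 0.127 × 2.522 ≈ 0.32 LAZ, above the 0.3 set for full exposure.

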### Ethics and dissemination

Ethical approval was obtained from the International Food Policy Research Institute (IFPRI) Institutional Review Board, and from the African Medical Research Foundation Ethics and Scientific Review Committee in Kenya, and has been updated with changes in the protocol after commencement. Approval of changes to protocol modifications are submitted to the same. Adverse effects, while not anticipated, would be reported to both of these bodies immediately.

Identifiers will be used to uniquely identify individuals and households. Once the data sets have been created, any information allowing the identification of an individual or household (such as names and address) will be stripped from the data sets and destroyed. Any information allowing the identification of individuals or households will be destroyed. Any information obtained in connection with this study will be used in a manner that does not publicly disclose any participant’s identity and will be kept confidential. Only study investigators will have access to the final data set.

Serum aflatoxin levels at enrollment are reported back to participants during village-level dissemination meetings and household visits several months later. Summary statistics of the baseline blood and maize aflatoxin results have been reported to the Kenyan Ministry of Agriculture, Ministry of Health, and to the Meru and Tharaka-Nithi County administration offices. Full results will be provided to the same government bodies, and submitted for publication in peer-reviewed journals. Eligibility for authorship will be based on substantive contribution in three of five of the following areas: inception, fundraising, data collection, analysis, and manuscript preparation.

## Discussion

This protocol describes the first randomized controlled trial (RCT) to test for a causal impact of aflatoxin exposure on child growth. Given the strength of this relationship in published observational studies, the hypothesized health burden associated with an impact on growth, if present, would almost certainly exceed the known burden due to liver cancer and acute toxicity. Whether or not such relationship is found, results of the trial will have implications for the prioritization of aflatoxin control efforts by governments in affected regions, as well as international donors, which have been investing heavily in aflatoxin control in recent years [22].

The strength of this study compared to previous work addressing the same question is its utilization of a randomized controlled design. This approach overcomes the problem of omitted variable bias: that is, the possibility that the observed relationship between aflatoxin exposure and impaired child growth is driven by confounders. In order to reduce aflatoxin exposure among those assigned to the control group, the intervention provides participants with opportunities to have their stored maize tested and replaced with aflatoxin-safe maize if contaminated, and to purchase aflatoxin-safe maize through local stockists. The primary risk to the study is a lack of demand for these services: if participants in the treatment group cannot be reached, or do not submit to having their stored maize tested and swapped each month, or if they purchase maize from non-study vendors, aflatoxin exposure may not be sufficiently reduced to impact child growth outcomes. A further risk is lack of information on serum aflatoxin throughout the 2-year study period. Due to budget constraints, serum aflatoxin levels are only collected at enrollment (from expectant mothers) and from children at one or two follow-up visits, depending on enrollment wave. The difference in aflatoxin exposure achieved through the intervention over the study period as a whole will be estimated using data on the proportion of stored maize swapped and the proportion of purchased maize obtained through study-affiliated stockists. Future trials using a similar design would ideally collect serum samples from all children at multiple points in time over the study period to more precisely estimate exposure.

## Trial status

At the time of submission, recruitment had been completed and the intervention was ongoing. Follow-up data collection had not yet begun.

## Abbreviations

ANCOVA: analysis of covariance
GIPSA: Grain Inspection, Packers and Stockyards Administration
GPS: global positioning system
IARC: International Agency for Research on Cancer
IFPRI: International Food Policy Research Institute
HPLC: high-performance liquid chromatography
LAZ: length-for-age Z-score
MAICE: Mitigating Aflatoxin exposure to Improve Child growth in Eastern Kenya
MDE: minimum detectable effect
ppb: parts per billion
RCT: randomized controlled trial
SES: socio-economic status
SPIRIT: Standard Protocol Items: Recommendations for Interventional Trials
UK: United Kingdom
